## Sample size

The estimated sample size for the anticipated larger study was calculated using clinical outcome variables and using two-sided Z test statistics [43]. The final sample size calculation was computed using WINPEPI by Abramson (2004) [44]. The sample size calculation assumed and estimated that 20% of the individuals in the poorest quintile do not receive more than two antenatal care visits and are less likely to deliver by a skilled birth attendant in Cameroon [2–8]. Previous studies reported an approximately 10–15% increase in the use of antenatal care and a 10% increase in the use of skilled delivery [18–26]. Thus, the study assumes a 15% difference compared with the control assuming an inter-cluster coefficient of 0.001 [26, 45, 46], with four clusters. The study will need a sample size of 160 in each arm and a total of 320 individuals to obtain a 5% significance level and 80% power, assuming a loss to follow up of approximately 5%. The sample size when inflated yields 168 in each arm, a total of 84 in each group and a total of 42 in each cluster. Considering that this is a pilot feasibility study, the final sample size was determined by applying the criteria described by Wittes and Brittain (1990) [47] and Teere et al. (2014) [48] (if the sample size assumes a minimum compliance rate of 70% for the pilot RCT, a 50% sample size for the main trial is recommended, and Teere et al. (2014) also recommended a size of 60/group for a pilot study). Based on these recommendations for the pilot study, we defined a final sample size of 140 participants per arm, 70 in each group, and a total of 35 in each cluster. This sample size is large enough to meet the expectations of a pilot C-RCT and to account for potential loss to follow up.

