### Recruitment and follow up

Recruitment into the study will be prospective, and each participant will be followed during their pregnancy until they deliver. Mothers who do not deliver in the hospital will be followed-up in the community by community health workers within 1 week of delivery. The study will run for 18 months to allow time for the outcome to be measured and for enough participants to be enrolled in the study (this includes the formative phase). Recruitment is primarily based on referrals through community health workers, by word of mouth in the community, and through health-educational programs and healthcare workers in respective health clinics. Prior to introducing the intervention, community sensitization and the involvement of village leaders will be carried out in the health areas. Community meetings will be organized to explain the intervention to all community members through a brief pop-up presentation by the project lead and project coordinator. Furthermore, community health workers will be trained to inform all pregnant women about the intervention on an individual basis.

A total of eight community health workers will be involved in the project, two from each health area. Recruitment will occur within 8 months (allowing enough time for all women to deliver within the 18-month study time frame), and each community health worker will be responsible for recruiting approximately 35 pregnant women (approximately five women per month) to attain the estimated sample size. However, these districts have yearly deliveries totaling a minimum of 500 in Bali and over 1000 in the Ndop district [8]. Therefore, the estimated sample sizes are anticipated to be reached within a year. However, considering that all health areas within the district are eligible, the anticipated contingency plan for recruitment will be to recruit individuals from other health areas within the same district or divide the participating district into zones.

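### The pilot sample size contradicts itself: 140 per arm means 280 women, 35 in each of four clusters means 140, and the recruitment plan points to 280

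*Protocol article*

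**What the plan says.** For the larger study, the Sample size section of the protocol article assumes four clusters and derives 160 women per arm, 320 in all. After inflation for loss to follow-up this "yields 168 in each arm, a total of 84 in each group and a total of 42 in each cluster". It then cites two recommendations for sizing a pilot: half the main-trial sample, given a minimum compliance of 70%, and 60 per group. On the strength of both it states "we defined a final sample size of 140 participants per arm, 70 in each group, and a total of 35 in each cluster". No pilot total is given, and group is not distinguished from arm or from cluster.

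Under Stratification and randomization, each of the two districts contributes one intervention and one control health area. Allocation of health areas confirms that the health area is the unit randomised. Recruitment and follow up states "A total of eight community health workers will be involved in the project, two from each health area" and that "each community health worker will be responsible for recruiting approximately 35 pregnant women", at roughly five a month over 8 months. Steps in recruitment says that weekly recruitment continues up to the target size.

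**The concern.** A single sentence gives a per-arm size and a per-cluster size that differ by a factor of two once multiplied out. The number matters operationally because it is the point at which recruitment stops. It also sets how many phones and vouchers are needed: 70 or 140 phones for the intervention arm and, at five e-vouchers per woman, 350 or 700 e-vouchers. Enrolment rate is a primary feasibility outcome with a 50% threshold in Table 1, and the recruitment target is one natural reference for it. Finally, the rationale offered for the size does not lead to either total by any stated step.

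**Working it through.** **Inputs.** Two arms. Four clusters (Sample size), which agrees with two health areas in each of two districts and with eight workers at two per area (8 / 2 = 4). Main trial: 160 per arm, 320 total, then 168 per arm. Pilot: 140 per arm, 70 per group, 35 per cluster. Workers: 8, at about 35 women each.

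**1. The main-trial figure.** The inputs are "using two-sided Z test statistics", 5% significance, 80% power, a 20% base rate, and "the study assumes a 15% difference compared with the control assuming an inter-cluster coefficient of 0.001". The text does not say how the base rate enters, so I assume 20% versus 35%.
- Without continuity correction: n = [1.96·√(2·0.275·0.725) + 0.842·√(0.2·0.8 + 0.35·0.65)]² / 0.15² = 138 per arm.
- With continuity correction: 151 per arm.
- Design effect 1 + (m − 1)·0.001 applied to 151: 157 to 158 for m = 35 to 42, and 163 to 164 for m = 80 to 84.

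The stated 160 is reproduced to within 3%, and 160 × 1.05 = 168. Because the intracluster correlation is so small, this check cannot show whether a cluster was meant to hold 42 or 84 women. It does confirm that an arm is half the trial, since 160 per arm is stated to be 320 in total.

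**2. The pilot figure.**

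| Stated figure | Multiplied by | Total |
|---|---|---|
| 140 per arm | 2 arms | 280 |
| 70 per group, if group = health area | 4 | 280 |
| 70 per group, if group = arm | 2 | 140 |
| 35 per cluster | 4 health areas | 140 |
| 35 per worker | 8 workers | 280 |

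No reading of group makes all three figures in the sentence agree. If group means arm, as it does in Participants, in the description of the control group and in Table 2, then 70 contradicts 140 per arm. If it means health area, 70 contradicts 35 per cluster.

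**3. Recruitment pace.** Five women a month for 8 months is 40 per worker, which accommodates a quota of 35. A total of 140 would need only 140 / 8 = 17.5 women per worker, about 2.2 a month.

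**4. The main-trial line.** 2 × 168 = 336, but 4 × 42 = 168. If four clusters is the trial total, the consistent reading is 84 per health area (4 × 84 = 336) and 42 per worker (8 × 42 = 336).

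**5. The rationale.** Half of 336 is 168, and half of 320 is 160. Against 336, 280 is 83% and 140 is 42%. Against 320, they are 87.5% and 44%. On the other recommendation, 70 per group exceeds 60, but 60 inflated for 5% loss is 63 (60 × 1.05) or 64 (60 / 0.95), so no stated step arrives at 70.

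**6. The enrolment threshold, if measured against the target.** 50% of 140 is 70 women, and 50% of 280 is 140 women. Enrolment of 70 to 139 would pass against the first and fail against the second.

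**The case against.** The strongest reply is that the document itself favours one total. An arm is defined as half the trial, so 140 per arm is 280. The worker plan gives 280 independently, and the stated monthly pace fits it. Only the word cluster beside 35 is then wrong. This stands. A reader might infer that the two totals are equally supported and the target is undeterminable, but the text does not bear that out. It remains true that the sentence is wrong as printed.

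Three further replies also stand, at least in part.
- The 50% rule is not the only basis. The size is said to rest on both recommendations, and 70 per group satisfies the second. It would be wrong to say that the size has no support in the cited rules. It is fair to say that it is not the 50% and that the step to 70 is not shown.
- The 168/84/42 line concerns the larger study. Were its four clusters meant per arm, 168 / 4 = 42 and 168 / 2 = 84 would be exact. It needs clarifying, but it is not a proven slip.
- Table 1 names no denominator for the enrolment rate. It could be women screened, eligible or approached, so the effect on that criterion is conditional.

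**Conclusion.** The contradiction is real: the per-arm and per-cluster pilot sizes imply 280 and 140 women, a factor of two. This rests only on two arms and four randomised health areas, which three sections support. The likelier intent is 280, with 35 a per-worker quota, but only the sponsor can confirm it. Because recruitment runs to this target, it should be corrected before anyone relies on it.

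Two stronger inferences are not supported. One is that enrolling exactly 140 women would make the pilot both a success and a failure: 140 is 100% of one total and 50% of the other, which reaches a 50% threshold either way. Only 70 to 139 women would divide the readings, and only if the target is the denominator. The other is that the pilot misses an intended precision: the Sample size section states no precision target for the pilot.

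**What to change.** - Print one pilot total and a matching chain. On the document's own evidence this is 280 total = 140 per arm = 70 per health area = 35 per community health worker, with the per-cluster 35 removed.
- If 140 in total was meant, change 140 per arm to 70, keep 35 per health area, and reduce the worker quota in Recruitment and follow up to about 18, with the monthly pace to match.
- Define group once and use it consistently. Say whether the four clusters of the larger study are in total or per arm; if in total, restate 168/84/42 as 168 per arm, 84 per health area and 42 per worker.
- Restate the rationale: give the actual fraction of the main trial (83% or 42% of 336), and say that 60 per group is met and how 70 was reached.
- In Table 1, name the denominator of the enrolment rate and, if it is the target, which total.

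If 280 was intended, the cost is wording in the sample-size and recruitment text and one table row, with no change to the design. If 140 was intended, the workers' quota and pace change as well.

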## Enrolment

Voluntary informed consent will be collected from each study participant after screening for eligibility and randomization of the intervention and control areas. Consent will be obtained with a witness present in either written (language of choice) or oral form (if the participant is not literate). Individuals who are 13–17 years of age will provide consent with the addition of an assent form and a guardian based on context procedures for those within this age group. All participant medical records and personal information will be kept confidential to ensure privacy during the study. Only certified healthcare providers participating in the trial and project leads will have access to confidential records. The other project team members will have access to vital medical information pertaining to the trial, but another private participant information will be inaccessible.

### Allocation of health areas

Women attending the antenatal clinic and those identified by a community health worker will be screened for eligibility using a poverty assessment scale that will be employed within the study and incorporated into the Magpi data collection software (https://home.magpi.com/). Standard poverty assessment tools [49] will guide the development and adaption of the final tool to be employed. However, the study will consider contextual approaches of identifying those considered “poor” within the respective communities. Community health workers will help in identifying eligible pregnant women but will be blinded to the cutoff poverty scale that will be employed within the study for inclusion. The project team will decide on the cutoff for poverty eligibility, which will be primarily determined and informed by the formative study, taking context into consideration. Those individuals who are eligible and provide informed consent will be allocated to their respective groups by the project lead and/or coordinator. Upon entering the trial, participants will be aware of their intervention because the randomization is performed at the level of the health area, and it will not be possible to blind the participants.

### Steps in recruitment

Once a woman is identified by a community health worker to be pregnant, she will be asked a series of pre-eligibility questions after providing informed consent using the recruitment text. The woman will be allowed to ask questions to ensure that she has fully understood the project. Once the woman demonstrates an understanding of the informed consent form that will be administered by either the project lead or project coordinator, she will be asked to sign the form. A set of questions will be administered to screen for eligibility in terms of poverty assessment. These questions will be uploaded into Magpi, which will enable the project lead and coordinator to view the responses. For women who are identified by healthcare workers, a community health worker and project coordinator will follow up at home to administer the eligibility questions and to record the GPS location. Once a woman is identified by the project lead and coordinator to be eligible, the participant is reported to the community health worker or provider. Women will be recruited on a weekly basis until the sample size is attained. Once the participants are enrolled, they will be given a unique identifier number by the healthcare provider; in addition, a phone and a solar charger will be assigned to the woman in the intervention areas.

### Recruitment and follow up

Recruitment into the study will be prospective, and each participant will be followed during their pregnancy until they deliver. Mothers who do not deliver in the hospital will be followed-up in the community by community health workers within 1 week of delivery. The study will run for 18 months to allow time for the outcome to be measured and for enough participants to be enrolled in the study (this includes the formative phase). Recruitment is primarily based on referrals through community health workers, by word of mouth in the community, and through health-educational programs and healthcare workers in respective health clinics. Prior to introducing the intervention, community sensitization and the involvement of village leaders will be carried out in the health areas. Community meetings will be organized to explain the intervention to all community members through a brief pop-up presentation by the project lead and project coordinator. Furthermore, community health workers will be trained to inform all pregnant women about the intervention on an individual basis.

A total of eight community health workers will be involved in the project, two from each health area. Recruitment will occur within 8 months (allowing enough time for all women to deliver within the 18-month study time frame), and each community health worker will be responsible for recruiting approximately 35 pregnant women (approximately five women per month) to attain the estimated sample size. However, these districts have yearly deliveries totaling a minimum of 500 in Bali and over 1000 in the Ndop district [8]. Therefore, the estimated sample sizes are anticipated to be reached within a year. However, considering that all health areas within the district are eligible, the anticipated contingency plan for recruitment will be to recruit individuals from other health areas within the same district or divide the participating district into zones.

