#### Phase II: protocol for cluster randomized trial of electronic vouchers and a mobile application

##### Objective

To determine the feasibility of conducting a cluster randomized trial to increase access and utilization of antenatal care, skilled birth delivery, and family planning awareness by assessing the processes involved, management of resources, the mobile phone application software, and resources used.
i.Stratification and randomization

We will stratify health areas according to their equity scores (a higher equity score defines how remote or rural the area is, the distance from the district health service, and the enclaved nature of the topography with poor accessibility). Therefore, health areas with equity scores of ≥ 40 in the two participating health districts (Bali and Ndop) will be included. The second stage of stratification involves health areas with equity scores of ≥ 40 with a medicalized health center. All health areas with equity scores of ≥ 40 with no medicalized health center will be excluded at this stage. A medicalized health center implies the presence of a physician. Three health areas in Ndop meet the inclusion criteria with a ≥ 40 equity score and a medicalized center, namely Bambalang, Babesi, and Balikumbat. However, considering that the study requires two health areas, one for intervention and one for control, Balikumbat (equity score 42) will be excluded because it has a lower equity score than Bambalang (equity score 47) and Babesi (equity score 47). Bambalang and Babesi will be further randomized into a control and intervention health area via computer number generation. In the Bali district, Bosa and Nakka had the highest equity scores and had a medicalized center.

After stratification, a health facility assessment will be conducted to ensure the quality of health facilities for the intervention using the WHO Service Availability and Readiness Assessment (SARA) tool [42]. Health facilities will be assessed using this tool based on the context of Cameroon to ensure the quality of the services to be delivered and to ensure that all facilities are of equal standard and have the minimum required services to deliver the intervention, followed by the randomization of health areas into intervention and control groups using computer number generation (Fig. 2).

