#### Quantitative

After enrolment, community health workers will follow up with women on a weekly basis. We anticipate that performance bias will be reduced considering that the outcome is objective, and we also anticipate that detection bias will be reduced by blinding the statistician and data collectors. Providers, community health workers, and patients (pregnant women) will not be blinded because this is not possible due to the nature of the intervention. Selection bias will be eliminated through random assignment. Attrition bias may be likely in the control group because women in the control group may want to drop out of the study or refrain from providing or responding to questions during subsequent visits, especially because they will not be provided any mobile phones. To minimize this bias, we will sensitize the community through stakeholder meetings on the importance of the control group to encourage participation. To control for contamination, e-vouchers will be used, as the women will not be able to sell, misplace, or share their vouchers. Additionally, the use of equity scores as a baseline cutoff for rural or remote rural areas will help to control for contamination, as the health areas are far from each other. Prior to enrolment, the community sensitization, stakeholder meetings, and education programs will be performed to help increase compliance in the control group and prevent women from becoming unresponsive during the trial. We anticipate minimal loss to follow up due to the nature of the exposure (pregnancy) and outcome (antenatal care and skilled birth delivery).

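### The recruitment contingency contradicts the health-area selection rules and gives no allocation rule for the areas or zones it would add

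*Protocol article*

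**What the plan says.** Two parts of the protocol article describe who may be recruited.

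- **Phase II, Objective, item i (Stratification and randomization).** The first filter is that "health areas with equity scores of ≥ 40 in the two participating health districts (Bali and Ndop) will be included". The second is "All health areas with equity scores of ≥ 40 with no medicalized health center will be excluded at this stage". The section then reports that "Three health areas in Ndop meet the inclusion criteria with a ≥ 40 equity score and a medicalized center". Balikumbat (score 42) is dropped because only two areas are needed and Bambalang and Babesi both score 47. Bosa and Nakka are named for Bali. Facilities are assessed with the WHO readiness tool, and the areas are then randomised by computer.
- **Recruitment and follow up.** Eight community health workers, two per area, recruit over 8 months. The target is supported by the statement that "these districts have yearly deliveries totaling a minimum of 500 in Bali and over 1000 in the Ndop district". The fallback begins "considering that all health areas within the district are eligible" and is to "recruit individuals from other health areas within the same district or divide the participating district into zones".

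Three other places bear on this. Allocation of health areas puts randomisation at health-area level and has the project lead or coordinator allocate consenting women to their groups. Addressing sources of bias (Quantitative) relies on random assignment against selection bias, and says the equity cutoff "will help to control for contamination, as the health areas are far from each other". Table 1 makes enrolment within 6 months a feasibility outcome with a 50% threshold.

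**The concern.** The two recruitment rules cannot both stand. Either the areas are restricted to those that pass the equity, physician and facility checks and are then randomised, or every area in the district is open. Followed as written, the fallback could bring in women from areas that were never randomised and need not have passed those checks.

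Three things are at stake:

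- For the added women, the claim that random assignment removes selection bias has nothing behind it.
- Zones cut from a district need not be far apart, yet distance is one of the stated protections against contamination.
- The pilot is meant to show whether areas of this kind can supply enough women. Filling the quota from elsewhere could hide the answer.

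**Working it through.** **1. The plan's own target.** Eight workers × 35 women = 280 = 2 arms × 140. With two areas per district and two workers per area, that is 2 × 2 × 35 = 140 women per district. Sample size also gives 35 per cluster, and 4 × 35 = 140 in total, or 70 per district. Both readings are carried below.

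**2. Which areas could be added.**

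| District | Meet both criteria | Used | Left for the contingency |
|---|---|---|---|
| Ndop | 3 | 2 | 3 − 2 = 1 (Balikumbat); every other area fails at least one criterion |
| Bali | not stated; the two named areas have the highest scores and a physician-staffed centre | 2 | unknown; others may or may not qualify |

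So the statement that all areas are eligible is false for Ndop by the plan's own count. It is unsupported for Bali.

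**3. Allocation.** In a randomised area, a woman's arm follows from where she lives. For an added area or a new zone, no text says that it would be randomised, when, or by whom.

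**4. Possible bias if added women are pooled.** Suppose all added women fall in one arm, make up a share *f* of it, and differ from the rest by *d* points in underlying rate. The bias is then *f × d*. With *f* = 25% and *d* = 10 points it is 2.5 points. Over *f* = 10% to 50% and *d* = 5 to 20 points it runs from 0.5 to 10 points. The document gives neither *f* nor *d*; both are assumptions.

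**5. Enrolment outcome.** Table 1 counts enrolment within 6 months, and recruitment lasts 8 months. A top-up starting in months 1 to 6 would enter the measure; one starting later would not. No trigger date is stated.

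**6. The forecast.** Yield in the two areas of a district = *D* × (*t*/12) × *a* × *p*. Here *D* is yearly district deliveries, *t* the months of conceptions available, *a* the share of deliveries in the two areas, and *p* the share who are poor enough and consent. An 8-month window gives *t* = 8. Counting women already up to 4 months pregnant at opening gives up to *t* = 12. The required *a × p* at the stated minimum deliveries is:

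| | Pool, *t* = 8 to 12 | Need 140 | Need 70 |
|---|---|---|---|
| Bali, *D* = 500 | 333 to 500 | 42% to 28% | 21% to 14% |
| Ndop, *D* = 1000 | 667 to 1000 | 21% to 14% | 10.5% to 7% |

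The delivery counts are floors. Against the stated populations they are 500/73,614 = 6.8 and 1000/218,505 = 4.6 per 1,000 people, which may mean a partial count. If the birth rate were 20 to 40 per 1,000 (an assumption), Bali would have about 1,472 to 2,945 births a year, or about 981 to 1,963 in 8 months. A need of 140 would then be about 14% to 7%. Since *a* and *p* appear nowhere, the forecast can be neither confirmed nor refuted.

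**The case against.** The strongest reply is that silence about allocation is not a plan to allocate non-randomly. Area-level randomisation is the stated rule, and the coordinator's role may be no more than placing each woman in her area's group. A reader might infer that the contingency destroys the trial's randomised comparison, or that staff would choose the arm. The document supports neither: it gives no rule, and women in the four selected areas are unaffected. What stands is that the text provides no randomisation for anyone else.

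Other stronger readings also fail:

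- *Every outside area is barred by the criteria.* Balikumbat passed both and was dropped only for number, and the status of other Bali areas is not given.
- *Contamination control collapses.* Non-transferable e-vouchers and the bar on control women downloading the app do not depend on distance. Other health areas may be distant too, so the distance problem belongs mainly to the zone option.
- *The contingency will probably be needed because only 20% of women are poor enough.* The 20% in Sample size is the proportion within the poorest quintile with no more than two antenatal visits. It is not a poverty rate, and the poverty cutoff is left to the formative study.

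It can also be said that this is a pilot, with clinical outcomes planned for the larger study and summarised descriptively. That limits the harm to clinical results. It does not protect the enrolment, randomisation and contamination measures, which are the pilot's primary feasibility outcomes.

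**Conclusion.** The contradiction is real and rests on the text alone. The fallback treats all areas as eligible, while the selection section restricts them, and no allocation rule covers what would be added. The consequence is confined to women recruited outside the four selected areas, who would have no randomised comparison. Weaker contamination control follows chiefly if zones are used. A masked enrolment shortfall follows only if the top-up begins inside the 6-month window.

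No size can be fixed from the document. The bias range of 0.5 to 10 points is an illustration under assumed shares and rate differences, with all added women in one arm. The forecast is poorly founded because it uses district totals for two-area recruitment, but the probability that the fallback would be used is unknown. The matter should be settled before recruitment, because missing random allocation cannot be repaired afterwards.

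**What to change.** In Recruitment and follow up:

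- Delete the claim that all health areas are eligible, and delete the zone option.
- State that only women from the four randomised areas count in the enrolment-rate outcome and in between-arm summaries.
- If areas must be added, allow only those that meet the equity and physician criteria and pass the facility assessment. Assign the arm by computer before any woman there is approached, and report these areas separately. Assignment would have to be single where no pair exists, as in Ndop, where one qualifying area remains.
- Base the forecast on the four areas' own deliveries and the expected eligible share.

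This is a change of wording. Its cost is that the pilot may report a lower enrolment figure, which is itself a useful result. Lengthening recruitment is not a free alternative, since it would press against the 18-month study period and the September 2019 close in Table 2.
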